A cohort of children will be enrolled to assess the impact of the intervention on malaria. A minimum of 40 children per cluster (range 40 to 75), depending on cluster size, will be randomly selected, stratified by age and invited to participate in the clinical and travel/residence surveys and passive case detection (PCD). The random sample will be stratified by age so that approximately equal numbers of children below and above 36 months will be invited into the study. This was done in case there were marked differences in clinical malaria associated with the different age groups and to ensure balance between the 2 study arms. No distinctions in the sampling scheme will be made regarding gender, ethnic group, medical condition or physical health. Children will only be included on the condition that their carers/parents give witnessed informed written consent. Assurance will also be sought from carers/parents that they expect that the child will remain resident in their village during the transmission season and will not be sent away. If informed consent is not provided for a randomly selected child then replacement children will be randomly selected from those remaining in the village.

The impact of the intervention on the density of malaria vectors and their infection rate with malaria sporozoites will be measured in each village cluster. In each cluster 6 compounds will be selected randomly, from those that have consented to join the study and have at least 4 houses. In each household a room with a single adult male sleeper will be selected if the room owner/sleeper provides witnessed, verbal consent.

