**Schematic representation of the trial.**

### Randomisation

In cluster-randomised controlled trials it is particularly important to minimize imbalance for factors known to be highly correlated with the disease outcome - in this case age and location. In each cluster, children will be enrolled with equal numbers of children aged 6 to 35 months and 36 to 60 months, and children who drop out of the study in year 2 will be replaced, as far as possible, by children of a similar age. At each step of the wedge, clusters will be selected, as far as possible, to maintain an even balance of children in the 2 age groups. Balanced randomization will be used to ensure that, within each health centre catchment area, half of village clusters will have PPF-LLIN and half LLINs by the end of July 2014.

Stratified randomisation of village-cluster to the trial arms, as outlined above, will reduce some imbalances between these but, as only a relatively small number of units can be randomized in such a cluster design, it is important to assess baseline levels of malaria and known confounders. Baseline data parasite rates and anaemia collected from enrolled children in each cluster in May 2014 will be used to assess imbalances in malaria at the village-cluster level.

Observer bias will be reduced where feasible. Both types of nets will be of a similar shape and colour. As well as using RDTs, blood films will be read by microscopists blinded to the identity and intervention status of the subjects. Mosquito collector bias will be reduced by using standard Centers for Disease Control and Prevention (CDC) miniature light traps, which do not rely on the ability of the fieldworker to collect specimens. Trap catches will be examined by a different person to the trap collector and they will be blinded to the trap location and intervention status. The processes of the intervention, both for PPF-LLIN and LLINs, will be monitored closely not only for quality but also to document any bias between the clusters.

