### Study procedures and evaluations

LLIN distribution will be completed in mid-2014. Study nurses and field assistants will be provided with refresher training on diagnosis of malaria, the use of RDT and study procedures in 2014 and 2015 before the transmission season.

The compound of each study child will be geo-referenced using a hand-held global positioning system, as the primary data analysis has a spatial component. Travel/residence of cohort children will be assessed at monthly intervals on brief questionnaires to estimate their time at risk, and their bed net usage will be assessed at the same time.

Thick blood films will be stained with Giemsa and examined under 1000-fold magnification by trained, experienced microscopists. Parasite counts will be recorded per high power field and 100 fields will be counted before a slide is declared negative. Parasite density will be estimated assuming that one parasite per high power field equals 500 parasites/μL [34]. 2 slides will be prepared from each subject and read separately by 2 experienced microscopists; discrepancies in positive and negative reads and those greater than 10-fold between the 2 reads will be resolved by the microscopy supervisor. Field staff will deliver all CRF to the study physician within 2 days of the clinical attack or survey date. The study physician will check all CRFs weekly for completion and data consistency.

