### Outcome 1 – malaria morbidity

The primary endpoint is a comparison of the incidence of clinical episodes of malaria in children in the 2 intervention groups, measured by PCD. After a case of malaria is treated, time of observation will be censored for 3 weeks and further attacks of malaria during this period are not considered. History of travel away from the village for periods of over a week will be captured by the monthly surveys and time at risk will be censored for such periods. In addition, malaria cases in children who resided outside their study village for more than half the elapsed study period at the time of illness will be censored. An initial analysis will compare the incidence rates between the 2 intervention groups, adjusted for duration of sleeping under a PPF-LLIN. However, the main endpoint analysis will also adjust for distance between village clusters with different types of nets [38]. This adjustment is critical since the impact of PPF-LLIN is likely to increase as they cover larger areas and so reduce the spill over of mosquitoes from villages with LLINs. Specifically, a village with PPF-LLIN surrounded by other villages with PPF-LLIN is likely to be better protected against malaria than a village with PPF-LLIN surrounded by villages with LLINs. Since the replacement of drop-out individuals may introduce bias we will repeat the primary analysis including and excluding this group.

Each of the outcome measures collected in this study will be analysed using multi-level statistical modelling methods, with appropriate distributional assumptions (for example, logistic, Poisson or negative binomial for counts and rates, normal for biochemical measures, and so forth). Within each model, effect size (that is, difference between PPF-LLIN and LLIN clusters) will, as appropriate, be adjusted for clustering within the groups of villages, the shortest distance between each PPF-LLIN cluster of villages and its nearest control, LLIN, village-cluster, the time of use of current nets (to account for different times in PPF-LLIN and LLIN conditions for each group of villages), village-cluster size, sex distribution, house design, bed net use, and other relevant potential confounding factors. Effect sizes will be presented as mean differences or rate differences/ratios as appropriate, with 95% confidence intervals.

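### The outcome-model covariate list names bed net use, measured after allocation, but leaves age, the health-centre stratum and baseline malaria to an open clause

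*Protocol article*

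**What the plan says.** The Analytical plan promises both a per-protocol and an intention-to-treat analysis. Under Outcome 1 – malaria morbidity, the covariate sentence opens with "Within each model, effect size (that is, difference between PPF-LLIN and LLIN clusters) will, as appropriate, be adjusted for clustering within the groups of villages". It continues with a distance term, "the shortest distance between each PPF-LLIN cluster of villages and its nearest control, LLIN, village-cluster", and the time the current nets have been in use, and ends with "village-cluster size, sex distribution, house design, bed net use, and other relevant potential confounding factors". The sentence covers every outcome model. It does not say which of the two analyses carries which covariates.

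Other sections bear on that list:

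- **Randomisation** states the aim to "minimize imbalance for factors known to be highly correlated with the disease outcome - in this case age and location", and says "Balanced randomization will be used to ensure that, within each health centre catchment area, half of village clusters will have PPF-LLIN".
- **Randomisation** also says that the May 2014 parasite and anaemia data "will be used to assess imbalances in malaria at the village-cluster level". It states no adjustment.
- **Study area and participant eligibility** says "The random sample will be stratified by age so that approximately equal numbers of children below and above 36 months will be invited".
- **Study procedures and evaluations** describes monthly travel and residence questionnaires for cohort children and adds that "their bed net usage will be assessed at the same time". The Interventions section places this monitoring in the 2014 and 2015 transmission seasons.
- **Secondary endpoints** names age, with house design and bed net use, as an individual-level covariate for the linear and logistic regressions.

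**The concern.** Two features of the list pull in the wrong direction.

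First, it names a variable measured after allocation. Net use under a given net type is observed only once that net has been handed out. If families use one type more than the other, part of the effect of providing PPF-LLINs runs through use. Adjusting for use then removes that part, and the result no longer answers the intention-to-treat question.

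Second, it does not name the factors that the protocol itself ranks highest. Health centre is the stratum within which allocation is balanced, and the health facilities are where the primary cases are detected. Age stratifies the cohort sample and is named for other outcomes. Baseline parasite rate is collected in every cluster but is given only a descriptive role. Leaving these to a general clause allows the primary covariate set to be settled after imbalances have been seen.

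**Working it through.** **1. The plan's own figure.** Inputs from the Sample size rationale: rates 1.5 and 1.125 episodes per child-year, between-cluster coefficient of variation 0.25, 50 children for 2 seasons (taken as 100 child-years per cluster), 90% power, 5% significance (taken as two-sided).

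- Poisson part: (1.5 + 1.125)/100 = 0.02625
- Between-cluster part: 0.25² × (1.5² + 1.125²) = 0.0625 × 3.5156 = 0.2197
- Clusters per arm: 1 + (1.960 + 1.282)² × (0.02625 + 0.2197)/0.375² = 19.38

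This matches the stated 19.38. No covariate enters it, so the choice of covariates makes no stated figure wrong.

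**2. Bed net use.** The documents give no use by net type, so this is an illustration. Assumptions: personal use halves a child's rate (borrowing the 50% LLIN effect from the Sample size rationale); PPF-LLIN multiplies the rate by 0.75 at equal use; use under LLINs is 80%.

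Intention-to-treat ratio = 0.75 × (1 − 0.5 × use under PPF-LLIN)/(1 − 0.5 × 0.8)

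| Use under PPF-LLIN | Intention-to-treat ratio | Use-adjusted ratio |
|---|---|---|
| 60% | 0.875 | 0.75 |
| 70% | 0.813 | 0.75 |
| 80% | 0.750 | 0.75 |
| 90% | 0.688 | 0.75 |

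Adjustment overstates the benefit of providing the net if use falls, understates it if use rises, and changes nothing if use is equal.

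**3. Precision from baseline malaria.** Assumed layout: 40 clusters; 5 exchanged at the start of each month from June to September in each year; 14 surveillance months (June to December, twice); 50 children per cluster; the planning rates spread evenly over 7 months; month effects; a cluster random intercept with coefficient of variation 0.25. A cluster covariate with correlation r is taken to multiply the between-cluster variance by 1 − r².

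| r (assumed) | SE of log rate ratio | Reduction |
|---|---|---|
| 0 | 0.0480 | – |
| 0.4 | 0.0476 | 0.8% |
| 0.6 | 0.0469 | 2.2% |

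Adding cluster-by-month variance of 0.0156 to 0.03 leaves the reduction between about 0.8% and 2.5%.

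**4. Age and calendar time.** The same layout gives these cluster-months:

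- PPF-LLIN 2014: 5 × (7 + 6 + 5 + 4) = 110
- PPF-LLIN 2015: 20 × 7 + 110 = 250, so 360 in total
- LLIN 2014: 280 − 110 = 170
- LLIN 2015: 280 − 250 = 30, so 200 in total

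The share falling in 2015 is 250/360 = 69% for PPF-LLIN and 30/200 = 15% for LLIN. If the cohort simply ages a year between seasons, PPF-LLIN child-time is 0.69 − 0.15 = 0.54 years older on average. This is an upper figure, because replacement of children who leave would reduce it.

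**The case against.** The strongest reply is that the list is neither closed nor binding. It applies where appropriate, covers all outcomes, and ends with a clause into which age, health centre and baseline malaria all fit. The article condenses a fuller protocol, and a final covariate list may stand there or in an analysis plan. This stands. A reader might infer that the primary model excludes these factors or ignores the randomisation strata. The text supports only that they are not named.

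The design also protects the comparison. Each cluster contributes time under both nets, the Design section says each cohort supplies its own pre-exchange baseline, and the model allows for clustering. Stable differences between health centres and in baseline endemicity are therefore largely absorbed. This stands too, and it explains the small gain in step 3. A reader might instead put the same correlations into the parallel-design formula and obtain power rising from about 91% to 94–98%. That formula treats the study as a simple cluster-randomised trial, so those figures do not carry over to the stepped analysis.

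The age shift is in substance a calendar-year imbalance. A period term would absorb most of it, and age alone would be a poor stand-in.

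On bed net use, the two nets look alike and are distributed in the same way, so use may not differ. That makes the distortion uncertain, but it cannot be ruled out in advance. What survives is that the list puts forward a possible mediator without limiting where it is used, while the factors the protocol treats as most prognostic are left to discretion.

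**Conclusion.** The point holds in limited form. The plan names a post-allocation variable as an adjustment to the effect size, and leaves age, the randomisation stratum and baseline malaria to an open, conditional clause.

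The consequence for the estimate depends on use differing by net type. Under the stated assumptions, the intention-to-treat ratio could lie anywhere from 0.875 to 0.688 while the adjusted ratio stays at 0.75. With equal use that gap is zero. The documents do not show that use will differ, so they do not support a claim that the adjustment necessarily biases the result.

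The case for naming the other factors rests mainly on fixing the model before the data are seen and on consistency with the randomisation. The precision gain from baseline malaria is about 1% to 2.5% of the standard error. The sample size is unaffected.

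**What to change.** Add a sentence to the Outcome 1 analysis stating that the primary intention-to-treat model includes health centre (6 levels), current age (time-updated), the cluster's May 2014 parasite prevalence and a calendar-period term. State that bed net use enters only the per-protocol or explanatory analysis.

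The variables are already collected, so the cost is wording. The downside is about 7 to 8 extra parameters with 40 clusters: 5 for health centre, 1 or 2 for age and 1 for baseline prevalence. The period term adds to that, at 1 for season or 13 for month. Only 6 of these (health centre and baseline prevalence) are estimated from differences between clusters.

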### Outcome 2 - malaria transmission

Differences in malaria transmission experienced in the 2 arms of the study will be estimated by comparing the EIR in village clusters between the 2 arms, adjusted for length of time under PPF-LLIN and distance between village clusters with the 2 different types of nets. Generalised estimating equations will be used to estimate differences in numbers of indoor mosquitoes, adjusting for repeated measures within clusters and possible covariates.

#### Secondary endpoints

For the secondary clinical endpoints we will compare: (i) mean Hb concentration in children at the end of the transmission seasons; (ii) incidence of malaria defined by history of fever or temperature ≥37.5 °C and a *P. falciparum* parasitaemia cut-off defined to give optimum sensitivity and specificity in this setting; (iii) parasite rates (sexual and asexual) in children at the end of the transmission seasons; (iv) number of children with enlarged spleens at the end of the transmission seasons; and (v) prevalence of anaemia (mild, moderate, severe). Anaemic statuses will be defined as: severe anaemia = Hb <5 g/dL, moderate anaemia = Hb range from 5 to <8 g/dL and mild anaemia = Hb range from 8 to <11 g/dL.

In general, all quantitative outcomes will be compared using appropriate summary statistics, such as mean differences or risk ratios. Hypothesis testing will be based on a 2-sample unpaired *t* test, adjusting for possible co-variates. If the data do not satisfy normality and constant variance assumptions, an appropriate non-parametric test will be applied. Both linear regression (for continuous variables such as Hb levels) and logistic regression (for dichotomous variables such as presence or absence of parasitaemia) will be used to quantify the group differences allowing for individual level covariates (such as age, house design, bed net use) using covariance structures that represent the appropriate level of clustering.

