**Figure 1 Fig1:**
[figure not shown]
**Step-wedge design for roll-out of bednets.** Permethrin-treated nets were given to all clusters in May 2014, followed by pyriproxyfen & permethrin treated nets (red) being rolled-out to different clusters in 2014 and 2015.

Clinical malaria will be recorded by study nurses using PCD methods during the rainy seasons in years 1 and 2. Parasites will be detected by rapid diagnostic tests (RDTs) and thick smears will be stained for confirmation and parasite counting by study staff. Treatment will follow government guidelines.

The study cohort will be surveyed for malaria indices (parasite prevalence, anaemia and spleen rate) at the beginning and end of both transmission seasons to generate data for the secondary endpoints. Where possible, at each malaria survey except the first, an average of 50 children from each village cluster who have not been enrolled in the cohort but are of a similar age will also be surveyed for these malaria indices. This additional group of children may better reflect the *Plasmodium falciparum* parasite rate in the population than children in the PCD cohort. Baseline data from the cohort will be used to compare the village clusters before the interventions, and the cohort from each village cluster provides its own baseline data before net exchange to PPF-LLIN. In addition, we will request anonymized medical records from the 6 health facilities located in the valley and use these to document clinical malaria in children aged 6 months to 5 years living in villages outside the study area. These children represent a further control group which can be used to track temporal changes in malaria incidence during the study period. If malaria declines in the study area in year 2, but not outside, we can be confident that the decline is due to the intervention, rather than confounding factors such as low rainfall. The end-of-season survey data will also be used to attempt to define a *P. falciparum* parasitaemia cut-off giving optimum sensitivity and specificity for malaria cases in this setting [21].

A schematic representation of the trial is shown in Figure 2.

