### Sample size rationale

#### Clinical

LLINs reduce malaria morbidity by approximately 50% [3]. The combined impact of using permethrin, a pyrethroid, and pyriproxyfen is unknown. If the effects were simply additive a mean reduction of 75% could be anticipated for PPF-LLIN (that is, LLINs alone will reduce incidence by 50%, and if we assume the pyriproxyfen alone may reduce the remaining 50% incidence by half, there would be a 75% reduction). However, the effects may be synergistic (for example, by having a mass killing effect). In order to change national guidelines on the use of LLINs we consider that PPF-LLIN should be at least 25% more effective than LLINs. A study of 3- to 60-month old children in Burkina Faso reported an incidence of clinical episodes of malaria of 1.5 episodes/child/year. Malaria incidence data for 2012 from villages in the Banfora region of Burkina Faso indicate the coefficient of variation (CV) for this study will be approximately 0.25. Regarding this study as a simple cluster-randomised controlled trial, assuming CV = 0.25 and that an average of 50 children will be monitored in each cluster for 2 seasons, the study will have 90% power to detect a 25% increase in protection with PPF-LLIN compared to LLINs (that is, a reduction in the incidence of clinical episodes of malaria from 1.5 to 1.125 episodes/child/year) at the 5% level of significance if there are 19.38 clusters in each arm [35]; we thus propose to recruit 20 village clusters into each arm of the study. Adjusting for a coefficient of up to 0.5 for the differences in cluster size (the data from Banfora cited above suggest that this CV will be much lower - approximately 15%), 20 clusters per study arm will still provide the study with 85% power [36].

Assuming prevalence of *P. falciparum* around 30% [37], 20 clusters in each arm and CV = 0.3, the study could detect a 30% reduction of prevalence, with 5% significance and 80% power, between the study arms if longitudinal cohorts for each cluster contain at least 45 children. Assuming mean Hb around 10.5g/dL, 20 clusters in each arm and CV = 0.1, the study could detect a difference of 1.0g/dL in mean Hb, with 5% significance and 80% power, between the study arms if at least 35 children were followed in each cluster .

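### May 2014 haemoglobin, measured in every cluster before any net exchange, is not pre-specified as a covariate for the haemoglobin endpoint, although between-cluster variation is about 95% of the variance in its sample size

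*Protocol article*

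**What the plan says.** Mean Hb at the end-of-season survey is the first secondary clinical endpoint (Study endpoints, Clinical). Hb is measured by finger prick in all surveyed children (Clinical evaluations).

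The protocol describes the baseline in two places. Under Design, "the cohort from each village cluster provides its own baseline data before net exchange to PPF-LLIN". Under Randomisation, "Baseline data parasite rates and anaemia collected from enrolled children in each cluster in May 2014 will be used to assess imbalances" between clusters. The first PPF-LLIN exchange follows the LLIN distribution by one month (Interventions), so the May 2014 survey precedes all exchange.

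Two parts of the Analytical plan bear on Hb:

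- Outcome 1 promises multi-level models for every outcome. The named adjustments are clustering, distance to the nearest LLIN cluster, time of use of current nets, cluster size, sex, house design and net use. An open clause for further relevant confounders follows.
- Secondary endpoints bases testing on a two-sample t test that may be adjusted for covariates it does not name. It adds linear regression "allowing for individual level covariates (such as age, house design, bed net use", with a covariance structure for clustering. This list is given as examples.

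Neither part names May 2014 Hb, for the child or for the cluster.

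The sample size text reads "Assuming mean Hb around 10.5g/dL, 20 clusters in each arm and CV = 0.1", and then "the study could detect a difference of 1.0g/dL in mean Hb, with 5% significance and 80% power", "if at least 35 children were followed in each cluster".

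**The concern.** With 20 clusters per arm and a between-cluster CV of 0.1, the Hb comparison is limited by differences between clusters and hardly at all by the number of children. Covariates that vary mainly within clusters can recover little of that. A pre-exchange measurement of the same outcome in the same clusters acts on the dominant term directly, and it is already being collected.

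If baseline Hb is used only to look for imbalance, two things follow. Precision that the data could supply may be lost. And because the protocol plans to inspect the baseline without fixing what it will do with it, the decision to adjust could come to depend on what the inspection shows.

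**Working it through.** **Inputs from the protocol** (Sample size rationale, Clinical): mean Hb 10.5 g/dL, difference 1.0 g/dL, CV k = 0.1, 20 clusters per arm, 35 children per cluster, 5% significance, 80% power.

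**Assumed, because not given:** two-sided test; direction upward (10.5 to 11.5 g/dL); within-cluster SD s; cluster-level correlation r between May 2014 and end-of-season Hb.

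**Step 1. Reproduce the stated power.** The usual formula for means in a cluster trial, without the small-sample addition of one cluster, is

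c = (1.96 + 0.84)² × [2s²/m + k²(μ0² + μ1²)] / (μ1 − μ0)².

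- Between-cluster term: 0.01 × (10.5² + 11.5²) = 0.01 × (110.25 + 132.25) = 2.425.
- Setting c = 20: total variance = 20 / 7.849 = 2.548.
- Within-cluster term: 2.548 − 2.425 = 0.123, so s = √(0.123 × 35 / 2) ≈ 1.47 g/dL.

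The stated 80% therefore reproduces with an SD near 1.5 g/dL. Variants at s = 1.5, all with one cluster added, give 77.9% (upward), 81.4% (common mean of 10.5) and 84.7% (downward to 9.5). With one cluster added and 100 child-seasons per cluster, the rate version of the formula also returns the protocol's 19.38 clusters for the primary endpoint.

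**Step 2. Between-cluster share of the variance.**

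| s (g/dL) | 2s²/35 | Share = 2.425 / (2.425 + 2s²/35) |
|---|---|---|
| 1.0 | 0.057 | 97.7% |
| 1.5 | 0.129 | 95.0% |
| 2.0 | 0.229 | 91.4% |

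At s = 1.5 the share is 94.5% with a common mean of 10.5 and 94.0% with a fall to 9.5. The figure of about 95% is robust.

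**Step 3. What baseline adjustment could add.** Adjusting for a baseline with cluster-level correlation r multiplies the variance by about 1 − r². Starting from 80%, power = Φ(2.80 / √(1 − r²) − 1.96).

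| r | 1 − r² | Power | Gain (points) |
|---|---|---|---|
| 0.2 | 0.96 | 81.6% | 1.6 |
| 0.3 | 0.91 | 83.6% | 3.6 |
| 0.4 | 0.84 | 86.4% | 6.4 |
| 0.5 | 0.75 | 89.9% | 9.9 |
| 0.6 | 0.64 | 93.8% | 13.8 |
| 0.7 | 0.51 | 97.5% | 17.5 |

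If only the between-cluster term is reduced, with s = 1.47, the results are 81.5%, 83.4%, 86.1%, 89.4%, 93.3% and 97.0%. Reaching 90% by the first calculation needs r = 0.503.

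**Step 4. If December 2015 already serves as a reference.** All clusters hold PPF-LLIN by the end of September 2015 (Design). Suppose both December surveys enter one model with cluster effects, the net effect is constant and all correlations equal r. The variance factor is then 1 − r² without May 2014 and 1 − 2r²/(1 + r) with it.

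| r | Without May 2014 | With May 2014 | Gain (points) |
|---|---|---|---|
| 0.2 | 81.6% | 82.6% | 1.1 |
| 0.3 | 83.6% | 85.5% | 1.9 |
| 0.5 | 89.9% | 92.9% | 3.1 |
| 0.7 | 97.5% | 99.0% | 1.5 |

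Under those conditions May 2014 adds about 1 to 3 points.

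**The case against.** The strongest reply is that nothing in the text rules the adjustment out. The t test may be adjusted, the regression covariates are examples, and the general model has an open clause. A protocol article need not list every covariate of a secondary model. This part stands: a reader might infer that the Hb analysis is unadjusted or excludes baseline Hb, and the documents do not support that. What remains is that the article does commit itself to a test, to named covariates and to a stated role for the baseline, and leaves the most useful covariate out of all three. The Design remark that each cluster supplies its own baseline points towards own-baseline comparison, but no model takes it up.

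A second reply is that December 2015 already gives each cluster a reference, so May 2014 adds little. This shrinks the possible gain, as step 4 shows, but does not remove it. It needs a pooled model that the Secondary endpoints text does not specify for Hb. It also needs a constant effect, whereas Outcome 1 and the Discussion expect the effect to grow with coverage.

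A third reply is that not every child has a baseline. This is correct. The non-cohort children surveyed from the second survey on (about 50 per cluster on average) and the May 2015 replacements have no May 2014 value of their own. For them only the cluster mean is available.

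**Conclusion.** The point holds as one of pre-specification and forgone precision on a secondary endpoint. May 2014 Hb is available for the cohort in every cluster before exchange, is not named in either model description, and bears on about 95% of the variance in the Hb sample size (91% to 98% for an SD of 1.0 to 2.0 g/dL).

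The stated 80% power is not in error; it reproduces without any baseline adjustment. A reader might also infer that a fixed amount of power, say 10 points, is being given up. The documents do not support a single figure, because they give no correlation between May and end-of-season Hb, and 10 points requires r of about 0.5. Over r = 0.2 to 0.7 the gain runs from about 2 to 17 points for a single end-of-season contrast. It is about 1 to 3 points if both December surveys are pooled with cluster effects and the effect is constant.

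**What to change.** In the Secondary endpoints part of the Analytical plan, pre-specify for Hb a multi-level linear model of end-of-season Hb on net type. Adjust it for the cluster mean of May 2014 Hb and, for cohort children who have one, the child's own May 2014 value. Replacement and non-cohort children enter with the cluster mean alone.

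State which survey carries the contrast: either base it on December 2014, or include a survey term if December 2015 is pooled. No cluster holds LLINs in December 2015, so pooling without that term would mix net type with year.

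Take the reported estimate and p-value from this model. That also settles how the t test relates to the multi-level models promised under Outcome 1.

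The cost is wording and one or two degrees of freedom. No new data are needed.
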